**Methods:**

The study is a mixed-method randomized controlled trial to evaluate the effects of a 12-week intervention for adults with schizophrenia. The treatment group (30 participants) will receive the intervention in addition to standard care and the control group (30 participants) only standard care. The intervention consists of 24 biweekly sessions with a duration of 60 min. The pre-test (weeks from 4 to 2 prior to the intervention) and post-test (week 12) include clinical measure (PANSS), quality of life, social performance, movement quantity, brain function and eye tracking measures. In addition, a treatment subgroup of 12–15 participants and their family member or other next of kin will complete a qualitative interview as a part of their post-test. Two follow-up tests, including clinical, quality of life, brain function and eye tracking will be made at 6 and 12 months from the completion of the intervention to both study groups. The primary outcome is change in negative symptoms. Secondary outcome measures include general and positive symptoms, quality of life, social performance, movement quantity, brain function and eye tracking. Explorative outcome includes patient and family member or other next of kin interview.

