### 2.7. Sample size

The sample size is calculated according to the primary outcome PANSS. For the primary outcome (improved negative symptoms according to PANSS after 12 weeks), the total number of required study participants was calculated (Curcic et al., 2017). Calculation was based on a minimum improvement of 15% on total PANSS score between the intervention and control group. With a power of 80% and a significance level of 0.05, we calculated the sample size to be *N* = 60 (30 intervention + 30 control participants), including a 25% dropout rate.

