### 3.1. Primary outcome measure

#### 3.1.1. Positive and negative schizophrenia symptom scale (PANSS) negative symptoms subscale

The healthcare professional evaluates the patients with PANSS Negative Symptoms subscale (Cronbach’s alpha of 0.83, Kay et al., 1988; von Knorring and Lindström, 1992) at baseline, at week 6 at and after week 12, PANSS Negative Symptoms subscale will also be collected in the follow-up session; 6 and 12 months after finishing the intervention.

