#### 3.3.3. Statistical analysis

The InMotion study follows the intention-to-treat paradigm. Complementary analyses will be performed per protocol according to the number of sessions the participant attends. For baseline statistics between the groups, descriptions will be constructed using frequencies and proportions for categorical data and means and standard deviations for continuous variables. Baseline characteristics will be compared using the Fisher exact test for dichotomous outcomes, the Mantel-Haenszel chi-square test for ordered categorical outcomes, and the Mann-Whitney *U*-test or unpaired *t*-test for continuous outcomes. A *P*-value of < 0.05 for the two-tailed test will be considered statistically significant for all outcomes. When deemed necessary, correction for multiple significance will be performed.

The primary outcome analysis will initially be performed using a Fisher exact test to evaluate differences between groups. To analyze the change in scores from baseline between groups for approximately normally distributed variables, a repeated-measures covariance pattern mixed model will be used, adjusting for significant differences at baseline. To identify predictive factors at baseline that might be associated with the primary outcome, a univariable logistic regression analysis followed by a stepwise multiple logistic regression analysis will be performed.

The distribution of continuous variables will be described using the mean and standard deviation or median and interquartile range. Categorical variables will be described with numbers and percentages.

The interviews will be analyzed by qualitative content analysis, to this day planned to be according to Hsieh and Shannon (2005); data from interviews will be transcribed verbatim, read through and analyzed into units. These units will be condensed and coded. The codes will be divided into categories and subcategories, and abstracted to overall themes if found. Latent meaning will be interpreted and the themes shall capture the core message of the whole data-material and will be strengthened with quotes. NVivo software program (QSR International; NVivo, 2022) will be used during the analysis.

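### The named primary test, Fisher's exact test, does not fit the stated primary outcome, a change score with no responder definition, and the mixed model also planned for that score is left unranked.

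*Protocol article*

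**What the plan says.** The abstract of the protocol article states the outcome as a change: "The primary outcome is change in negative symptoms". Section 3.1.1 gives the instrument, "The healthcare professional evaluates the patients with PANSS Negative Symptoms subscale", with ratings at baseline, weeks 6 and 12, and 6 and 12 months after the intervention. Section 2.7 puts the primary time point at 12 weeks: "For the primary outcome (improved negative symptoms according to PANSS after 12 weeks), the total number of required study participants was calculated".

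Section 3.3.3 then makes four statements that bear on the analysis:

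- On the primary outcome: "The primary outcome analysis will initially be performed using a Fisher exact test to evaluate differences between groups".
- On scores: "To analyze the change in scores from baseline between groups for approximately normally distributed variables, a repeated-measures covariance pattern mixed model will be used".
- On predictors of the primary outcome: "a univariable logistic regression analysis followed by a stepwise multiple logistic regression analysis will be performed".
- On baseline comparisons: "Baseline characteristics will be compared using the Fisher exact test for dichotomous outcomes". Continuous variables there get a Mann-Whitney or unpaired t-test.

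The significance rule is general: "A *P*-value of < 0.05 for the two-tailed test will be considered statistically significant for all outcomes". Correction for multiple testing is left to discretion. No passage gives a per-patient threshold on the negative subscale.

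**The concern.** Fisher's test needs each patient classed as one of two things. The outcome described is a score on a multi-item scale, and the article never says what change makes a patient improved. The section itself uses the Fisher test for two-category variables and other tests for continuous ones, so the primary analysis departs from the section's own convention. The logistic regression on the primary outcome also needs a binary variable, so it shares the gap.

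Three things are at stake. First, the primary result may depend on a cut-point the article has not fixed, in a trial whose participants know their allocation. Second, cutting a score in two discards information, which matters with 60 patients. Third, the mixed model answers the same question by another route. If the two tests disagree, nothing in the article says which one is the trial's result.

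**Working it through.** **1. Is a responder definition given anywhere?** The nearest candidate is in section 2.7, which speaks of improved negative symptoms and a 15% minimum improvement. That 15% is on the total PANSS score, not the negative subscale, and is a difference between the groups, not a threshold for one patient. It does not supply the missing cut-off.

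**2. Can N = 60 be reproduced?** Not forwards: no SD, baseline mean or responder rate is given. Inputs from section 2.7 are 30 + 30 patients, 80% power, a significance level of 0.05 and 25% dropout; section 3.3.3 makes tests two-tailed. Evaluable patients: 60 × 0.75 = 45, or 22 to 23 per arm. Solving a comparison of means for the standardised difference:

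d = (1.960 + 0.842) × √(2/n)

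This gives 0.845 for n = 22, 0.835 for n = 22.5 and 0.826 for n = 23. Going back with d = 0.835 gives 23 per arm and 46/0.75 = 62 randomised (58 if 46 is multiplied by 1.25). A comparison of means with d of about 0.83 is therefore consistent with 60. Reading the 15% as a 15-point difference in responder proportions is not: for control rates of 1 to 50% it needs 54 to 170 per arm, or 144 to 454 in total with dropout.

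**3. What would dichotomising cost?** Assumptions, none stated in the article: the 80% belongs to a comparison of means, scores are normal, and the intervention shifts the distribution by d. If a fraction p of controls respond, the intervention fraction is Φ(Φ⁻¹(p) + d). Fisher power is the summed probability of all 2×2 tables with two-sided P < 0.05.

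| Control responders | Intervention responders (d = 0.835) | 22 per arm, d = 0.835 | 23 per arm, d = 0.845 | 30 per arm (no dropout), d = 0.835 |
|---|---|---|---|---|
| 5% | 21% | 23% | 25% | 27% |
| 10% | 33% | 35% | 38% | 47% |
| 20% | 50% | 43% | 47% | 59% |
| 30% | 62% | 46% | 51% | 63% |
| 34% (midpoint cut) | 66% | 46% | 51% | 64% |
| 50% | 80% | 43% | 47% | 59% |
| Comparison of means (t-test) | – | 77% | 80% | 89% |

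By normal approximation the comparison of means has 79%, 82% and 90% power in the three columns.

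For 80% Fisher power at the midpoint cut (66% against 34%), the continuity-corrected formula for two proportions gives 43 evaluable per arm, so 86/0.75 ≈ 115 randomised.

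**4. What would two unranked tests do to type I error?** Two independent tests at 0.05 give 1 − 0.95² = 9.75% as a reference. These two share the same data and are strongly correlated. I simulated 20,000 null trials per setting with 23 per arm, a baseline-to-follow-up correlation of 0.5 or 0.7, and one fixed cut-point on change. A baseline-adjusted comparison stood in for the mixed model. Fisher alone rejected in about 2.5%, the adjusted comparison in about 5%, and either one in about 6.4 to 6.7%.

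**The case against.** The strongest reply is that a binary outcome was intended. Section 2.7 speaks of improved symptoms, and the logistic regression presupposes a yes/no variable. This is a condensed article, and the full protocol and analysis plan are not shown, so a responder definition may exist there. That is fair, and it is why the point is that none is defined here, not that none could exist. It does not remove the mismatch: the article itself names a test and an outcome that do not fit together.

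Several stronger readings are tempting and are not supported:

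- **Power falls from 80% to about 40 to 50%.** A reader might take this as fact. Section 2.7 does not say what test the 80% refers to. If the sizing was done on responder proportions in some form, nothing falls from 80%.
- **The Fisher test conflicts with intention to treat.** It does not have to. Patients who drop out can be counted as non-responders, and missing-data rules are commonly left to the analysis plan.
- **The Fisher test ignores baseline.** A responder status defined on change uses the baseline value. The valid criticism is lost information.
- **There are two competing primary tests.** Only Fisher carries the primary label. The mixed model is stated for change scores in general and reaches the primary outcome by implication.
- **The cut-point will be chosen after the data are seen, or success on either test will be claimed.** The article says neither. Both are risks it leaves open.

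**Conclusion.** The point holds. The stated primary test does not match the stated primary outcome, no per-patient criterion connects them, and the logistic regression has the same gap. Two tests apply to the outcome with no ranking. This conclusion rests on the text alone and needs no numerical assumption.

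The sizes are conditional. Type I error of roughly 6 to 7% applies only if success on either test counts and one cut-point is fixed. The Fisher power of about 23 to 51% after the planned dropout, or at most about 64% with none, rests on a back-solved d of about 0.84, normal scores and the 80% belonging to a comparison of means. Under those assumptions the loss is large at every cut-point examined, but the article does not establish that the trial was sized that way.

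This should be corrected before group data are examined, because the primary analysis as written depends on a decision that could change the trial's conclusion.

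**What to change.** Make the repeated-measures mixed model already in section 3.3.3 the single primary analysis of the PANSS negative score. Adjust for the baseline PANSS negative score whether or not the groups differ on it. State that the deciding estimate is the treatment difference at week 12, with its 95% confidence interval, in all randomised patients.

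Remove the Fisher test from the primary analysis. If a responder proportion is wanted, define the per-patient cut-point on the negative subscale and the visit it applies to before any group data are seen, and label the comparison supportive. Use the same definition as the outcome of the logistic regression.

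Keeping a responder outcome as primary would also remove the contradiction, but it would need the definition stated and the sample size justified for that test. Under the assumptions above, that could mean about 115 randomised patients instead of 60.

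The recommended change costs wording only: the model is already planned and no new data, visits or patients are needed.

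### The mixed model takes as covariates only baseline variables that differ significantly between arms, so chance picks them and the baseline PANSS negative score is rarely adjusted for

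*Protocol article*

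**What the plan says.** Section 3.3.3 describes between-arm tests of baseline variables: "Baseline characteristics will be compared using the Fisher exact test for dichotomous outcomes", with a Mantel-Haenszel chi-square test for ordered categories and a Mann-Whitney or t-test for continuous variables. The threshold is P < 0.05 "for the two-tailed test will be considered statistically significant for all outcomes".

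The model for scores is then introduced by its purpose: "To analyze the change in scores from baseline between groups for approximately normally distributed variables". The method that the section gives for this purpose, with its rule for covariates, reads: "a repeated-measures covariance pattern mixed model will be used, adjusting for significant differences at baseline". No covariate is named as fixed. The response is change, so baseline enters by subtraction, but it becomes a regression covariate only if it passes the significance filter.

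Three other sections bear on this:
- Section 2.6 places randomization after the baseline measurements.
- Sections 2.3.1 and 2.3.2 set an entry floor of about 21 on the PANSS negative items, and section 3.1.1 measures that subscale at baseline. The score should exist for everyone.
- Section 2.11 lists seven background characteristics to be collected: gender, age, education, way of living, years since diagnosis, medication and smoking.

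**The concern.** A covariate earns its place in a randomized comparison by predicting the outcome. A between-arm test at baseline does not measure that. If allocation is sound, it flags one true null hypothesis in twenty. The stated rule therefore selects on chance imbalance, and it has three consequences.

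1. The final model cannot be written down before the data are seen.
2. Baseline PANSS negative, the obvious predictor of later PANSS negative, is usually handled by subtraction alone. That is less efficient than regression adjustment unless the correlation is close to 1.
3. An imbalance just short of significance is left in place, and regression to the mean can then add to or mask a treatment effect in that particular trial.

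This is a rule the article states, not a detail it leaves out. An analysis plan that fixed the covariates would have to override the published text. With 30 per arm and 25% dropout expected, precision given away for nothing matters.

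**Working it through.** **Inputs from the document.** N = 60 (30 + 30), 25% dropout, two-sided 0.05, 80% power (section 2.7). Evaluable: 60 × 0.75 = 45, or 22.5 per arm.

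**Assumptions, not in the document.** The baseline to follow-up correlation ρ, taken as 0.3 to 0.9; the effect in SD units; normal scores; one post-baseline visit.

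**The plan's own figure.** Section 2.7 gives no SD and no control mean, so N = 60 cannot be derived forward. Solving backwards, d = (1.960 + 0.842) × √(2/22.5) = 0.835. N = 60 fits an effect of that size, but this is not a reproduction.

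**How often the baseline score enters.** Under randomization, 5% by construction. Simulation gave 4.7 to 5.3%.

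**How predictable the model is.** With the seven characteristics of section 2.11, if the tests were independent, the chance that at least one enters is 1 − 0.95⁷ = 0.30.

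**Variance with equal baseline and follow-up SD (= 1).** Change score: 2(1 − ρ). Baseline-adjusted: 1 − ρ². The ratio is (1 + ρ)/2, that is 0.65, 0.75, 0.85 and 0.95 at ρ = 0.3, 0.5, 0.7 and 0.9.

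**Power, 22 per arm, true effect 0.7 SD (20,000 simulated trials per cell).**

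| ρ | never adjust | stated rule | always adjust | rule's loss (points) |
|---|---|---|---|---|
| 0.3 | 48.1% | 48.6% | 65.0% | 16 |
| 0.5 | 62.1% | 62.7% | 73.7% | 11 |
| 0.7 | 83.7% | 84.0% | 87.9% | 4 |

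Other runs of the same scenario put the middle loss at 11 to 12 points. At ρ = 0.9 the change score alone gives 0.7/√(0.2 × 2/22) = 5.2 standard errors, so power is near 100% either way.

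**Power with the effect scaled so that the unadjusted change score has 80% power by normal approximation (22 v 23 patients, 20,000 trials).** This removes the ceiling at high ρ.

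| ρ | never adjust | stated rule | always adjust | rule's loss (points) |
|---|---|---|---|---|
| 0.3 | 77.8% | 79.4% | 91.7% | 12 |
| 0.5 | 77.7% | 78.6% | 87.5% | 9 |
| 0.7 | 78.5% | 78.8% | 83.6% | 5 |
| 0.9 | 78.2% | 78.2% | 79.1% | 1 |

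In both tables the stated rule performs almost like never adjusting.

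**Effect of the entry floor.** Entry requires about 21 or more on the outcome scale itself, so baseline is truncated and follow-up is not. As an illustration, cut a normal score at the source-population median (an assumption). Baseline variance falls to v = 1 − 2/π = 0.363. With ρ the correlation before truncation, the adjusted-to-change variance ratio is (1 − ρ²)/[(1 − ρ)²v + 1 − ρ²]. At ρ = 0.3 this is 0.91/(0.49 × 0.363 + 0.91) = 0.84; at 0.5, 0.7 and 0.9 it is 0.89, 0.94 and 0.98. The loss at a 0.7 SD effect shrinks to roughly 5, 4 and 2 points at ρ = 0.3, 0.5 and 0.7, give or take a point or two between simulation runs.

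**Type I error of the stated rule.** 3.9 to 4.8% across the null simulations.

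**Imbalance left unadjusted.** With 30 per arm, baseline means must differ by about 2.00 × √(2/30) = 0.52 SD to reach P < 0.05. Given a smaller gap, the change-score contrast is shifted by (1 − ρ) × gap: up to about 0.36, 0.26 and 0.16 SD at ρ = 0.3, 0.5 and 0.7.

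**The case against.** The strongest reply concerns size. Neither ρ nor the effect comes from the document, the (1 + ρ)/2 ratio needs equal variances, and the entry floor breaks that condition in the direction that shrinks the loss. This stands. The equal-variance losses are not an estimate for this trial, and the cut point that governs the shrinkage is itself unknown. The simulations also use one post-baseline visit, while section 3.1.1 has four (weeks 6 and 12, months 6 and 12).

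A second reply is that baseline is not ignored. Subtraction uses it, and a longitudinal model with baseline as a response and a common baseline mean for both arms would lose little. That is true, but section 3.3.3 describes no such model; it describes change scores with conditional adjustment.

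Three stronger readings are tempting and not supported:
- **Data-driven selection inflates false positives.** The rule's type I error is at or slightly below 5%, so it is mildly conservative.
- **A covariate let in by chance biases the result.** It makes the model unpredictable. The 30% figure shows only that, and only if the tests are independent.
- **This is the primary analysis.** The section also says "The primary outcome analysis will initially be performed using a Fisher exact test to evaluate differences between groups", so it is unclear which analysis is primary. That needs settling separately.

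Reporting baseline P-values is a matter of presentation. The fault lies in using them to choose covariates.

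**Conclusion.** The point holds. The stated rule chooses covariates by chance imbalance, leaves the model open until the data are seen, and gives almost the same power as never adjusting. The harm is lost precision and uncorrected non-significant imbalance, not false-positive risk.

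The size is uncertain. Under equal variances, 22 per arm and a 0.7 SD effect, the loss runs from about 16 points of power at ρ = 0.3 to about 4 at 0.7 and close to none at 0.9. With the entry floor at the source median it is roughly 5 points down to 2 over ρ = 0.3 to 0.7. The direction does not depend on these choices: always adjusting did not reduce power in any case examined. The repair is worth making because it costs nothing, even if the gain is at the low end.

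**What to change.** In section 3.3.3, or in an analysis plan that expressly replaces it:

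- In the mixed model for PANSS negative, always include baseline PANSS negative and its interaction with visit as covariates.
- In each secondary outcome's model, always include that outcome's own baseline.
- Delete the clause that makes adjustment depend on significant baseline differences. Name any further covariates in advance on prognostic grounds.
- Describe baseline by arm, and do not use baseline tests to choose covariates.

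This needs no extra participants, visits or measurements. It should be done before anyone sees outcome data by arm, because afterwards the choice would be post hoc.

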### 1.5. Aims and expected results

The primary aim of the study is to investigate the effects of mixed exercise program with creative movement and cognitive, emotional and social stimulation as add-on to ongoing pharmacological treatment, in treating negative symptoms of schizophrenia. Previous studies with dance movement therapy, body psychotherapy or physical exercise show reduction in negative symptoms of schizophrenia (Röhricht et al., 2011; Lee et al., 2015; Martin et al., 2016; Gökcen et al., 2020), and that the change in these symptoms can be measured with PANSS (Röhricht et al., 2011; Lee et al., 2015; Sabe et al., 2020; but see but see also Bryl et al., 2020 for qualitative but not significant quantitative results). Thus, our hypothesis is that the intervention will improve negative symptoms detectable with PANSS in comparison to the control group. The reduction is anticipated to correlate with changes in brain function and physical measures. In line with previous studies (e.g., Röhricht et al., 2011; Lee et al., 2015; Curcic et al., 2017; Sabe et al., 2020), we will measure both negative and positive symptoms as well as general psychopathology, i.e., total PANSS score and look separately at the three symptom classes.

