### 2.11. Procedures

When a patient at the psychiatry clinic is interested in participating in the main study, contact information will be transferred from responsible clinician to doctoral student, who will call the participant, give further information, answer questions if needed, and check inclusion/exclusion criteria. A meeting at the movement laboratory at the hospital will be set up with participant and psychiatrist who will do the PANSS, CGI-S, CDSS, and PSP as well as the doctoral student who will conduct physical tests and measures and test cognitive function combined with functional brain imaging and eye tracking. The baseline measures will take about 2.5 h with a break in between. Data on gender, age, years of education, way of living, years with schizophrenia diagnosis, medication, and smoking will be collected but no other sociodemographic information. The baseline measurements will be conducted 4 to 2 weeks prior to the beginning of the intervention. It may take a few weeks to form a group, and therefore, a 2-week window for the baseline data collection is needed. The participant will be instructed about the accelerometer, which is to be worn for 7 days to evaluate everyday activity. After baseline measures are finished, sealed envelopes will be given to the participants to randomize whether they will be part of the control or intervention group. The participants in the intervention group will be shown videos of the instructors and the training studio, to enable recognition and feeling of safety.

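### Baseline predictors of a scale-score outcome are to be sought by univariable and stepwise logistic regression, with at most 30 participants in the smaller outcome class

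*Protocol article*

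**What the plan says.** Section 3.3.3 of the protocol article fixes both the model class and the selection strategy for the search for baseline predictors of the primary outcome: "a univariable logistic regression analysis followed by a stepwise multiple logistic regression analysis will be performed". It names no candidates and gives no entry or exit rule. The same section sets a 5% level "for the two-tailed test will be considered statistically significant for all outcomes" and leaves correction for multiple testing to discretion.

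The abstract defines the outcome as a change in score: "The primary outcome is change in negative symptoms". Section 3.1.1 and Table 2 identify the instrument as the PANSS negative subscale. No responder threshold appears anywhere in the article.

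Section 2.7 sets the size at 60 ("30 intervention + 30 control participants), including a 25% dropout rate"). Section 2.11 lists background data: "Data on gender, age, years of education, way of living, years with schizophrenia diagnosis, medication, and smoking will be collected". It does not call them candidate predictors.

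**The concern.** Logistic regression needs a yes/no outcome, and the primary outcome is not one. To run the planned analysis someone must choose a cut-off on the scale. If that happens after the data are seen, the choice is open to influence. Whenever it happens, cutting a score in two discards information in a trial that has little to spare.

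The smaller outcome class then limits how many candidates a logistic model can support. Screening factors one at a time and passing the survivors to a stepwise procedure uses the same few events twice. P-values, confidence intervals and coefficients from the final model are computed as if it had been chosen in advance, so retained effects tend to be too large and intervals too narrow. At stake is a published set of baseline predictors that may not replicate.

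**Working it through.** **Inputs from the protocol article.** 60 randomised, 25% dropout included (section 2.7); seven background factors (section 2.11); two-sided 5% level (section 3.3.3).

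**Assumed, because the article does not state them.** Responder rate 20-50%; the candidate list; the screening, entry and exit levels.

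**The plan's own figure.** The 60 cannot be re-derived, since section 2.7 gives no standard deviation or control mean. With 80% power, two-sided 5% and 22.5 completers per arm it corresponds to a standardised difference of (1.960 + 0.842) × √(2/22.5) = 0.835. A difference of 0.84 needs 23 per arm, 46 in total, and 46/0.75 = 61.3, so 62. The 60 is therefore not shown to be wrong, and it is taken as given here.

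**Events.**
- Completers: 60 × 0.75 = 45.
- Ceiling on the smaller class, whatever the cut-off: 60/2 = 30 with everyone analysed; 22 among 45 completers.
- Completers, 20-50% responders: 45 × 0.20 = 9; 45 × 0.50 = 22.5 (22 in whole participants).
- All 60, same rates: 60 × 0.20 = 12; 60 × 0.50 = 30.

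**Events per candidate = smaller class / number of candidates.**

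| Candidates | 45 completers | All 60 |
|---|---|---|
| 7 | 9/7 = 1.3 to 22.5/7 = 3.2 | 12/7 = 1.7 to 30/7 = 4.3 |
| 10 | 0.9 to 2.3 | 1.2 to 3.0 |
| 20 | 0.45 to 1.1 | 0.6 to 1.5 |

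The 10 and 20 rows show what happens if baseline measures from Table 2 join the list. Every entry is below 5.

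**Chance of a false predictor when none is real.** For k independent tests at 5% it is 1 − 0.95^k: 30% for k = 7, 34% for k = 8, 40% for k = 10, 64% for k = 20.

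Simulation of the two-step procedure (independent normal candidates, none related to outcome; assumed screen P < 0.20, then forward entry at P < 0.05; 600 data sets per setting; responder rates 20-49% at n = 45, and 20% and 50% at n = 60):

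| Candidates | At least one false predictor kept, n = 45 | n = 60 |
|---|---|---|
| 7 | 32-37% | 30-32% |
| 10 | 43-47% | 40-43% |
| 20 | 67-70% | 65-66% |

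Where a predictor was kept, the mean apparent area under the ROC curve was 0.71-0.81 at n = 45 and 0.68-0.76 at n = 60; the true value is 0.50. A separate run (1,500 data sets, n = 45, 8 candidates, 35% responders, the same screen, backward elimination at 0.05) kept at least one false predictor in 29%.

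**Reading the results.** The false-predictor rates are close to those of plain multiple testing, so they do not show large extra inflation from the stepwise step itself. The over-optimism shows in the apparent discrimination: a selected model looks useful when its predictors are pure noise.

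**The case against.** Much of the arithmetic rests on assumptions, and that stands. The article states no responder rate, so 9-22 events is not a trial fact. Intention-to-treat could bring in all 60. The seven background factors are only data to be collected, and the candidate list and selection rules may properly sit in an analysis plan that is not shown. None of this removes the point: the choice of univariable then stepwise logistic regression is stated, and the ceiling of 30 needs no assumption about responder rate.

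Three stronger readings are tempting but not supported.
- A reader might infer that the procedure is bound to yield false predictors, or that its output would be mostly noise. With 7-8 candidates and no true predictor, roughly 70% of simulated trials keep none, and the 29% is no higher than the 34% from eight plain tests.
- A reader might infer that the arms are pooled with no treatment term or interaction. Section 3.3.3 is silent on this. Its stated aim is association with the outcome; although it calls the factors predictive, it does not claim to identify who benefits.
- A reader might take section 2.7 to supply the missing cut-off: "Calculation was based on a minimum improvement of 15% on total PANSS score between the intervention and control group". That is a difference between groups on the total score, not an individual threshold on the negative subscale.

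It is also fair that this is a supporting analysis. It does not bear on the test of the main hypothesis, that "our hypothesis is that the intervention will improve negative symptoms detectable with PANSS in comparison to the control group". The cautions about secondary outcomes in section 7 do not mention it, however.

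**Conclusion.** The planned method is a poor choice for this outcome and this size of trial, and it is fixed in the text rather than left to a later document. The firm part is that the outcome is a scale score without a cut-off, and that the smaller class is at most 30 (22 among 45 completers), hence at most 4.3 events per candidate even for a list of only seven. The conditional part is 1.3 to 3.2 events per candidate among completers (20-50% responders assumed), and about a 30% chance of at least one false predictor with 7-8 candidates, rising to 65-70% with 20 (selection rules assumed, no true predictor). The result is likely, not certain, to be unstable and over-optimistic. The primary between-group comparison is untouched, so this is a change the sponsor should make but not one on which the main result depends.

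**What to change.** Replace the sentence in section 3.3.3 with a linear or mixed model on the continuous week-12 PANSS negative score, containing baseline score, treatment and two or three predictors named in advance, with no univariable screening and no stepwise selection. Report estimates with 95% confidence intervals and label the analysis exploratory. It can build on the repeated-measures mixed model already planned in that section.

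Describe the factors as associated with outcome, that is, prognostic. Claim that a factor predicts benefit from the intervention only if its interaction with treatment is tested, and state that such tests have low power at this size. Interactions also add tests: two or three predictors alone, each read at 5%, carry a false-positive chance of 1 − 0.95² = 10% to 1 − 0.95³ = 14%; with an interaction for each it is 1 − 0.95⁴ = 19% to 1 − 0.95⁶ = 26%. They are therefore optional.

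The change is one of wording and needs no new data. The price is that fewer candidate predictors can be examined.
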